### 3. **STUDY DESIGN**

This is a single-center, prospective, randomized double blind study. In total, 380 patients with a first acute MI will be included. All patients will be randomly assigned to receive metformin 500mg 2dd1 or placebo 2dd1 on top of standard medical care. The study will take place at the University Medical Center of Groningen, a center with experience in primary PCI of patients with acute MI and with access to emergency cardiac surgery.

CMR-imaging is performed to determine LVEF four months after PCI, a period in which the remodeling of the heart has completed. CMR is a well-recognized, validated, and highly reproducible technique. After long-term follow-up, metabolic, neurohormonal and novel markers, clinical endpoints, and left ventricular function will be assessed.

#### 4. STUDY FLOW CHART

[figure not shown]

## 5. STUDY POPULATION

### 5.1 Population

All patients with an acute STEMI admitted to the University Medical Center of Groningen who are amenable to PCI are considered for participation in the study. During the PCI procedure, patients will be asked for their verbal informed consent by the treating cardiologist and catheterization laboratory nurse (independent witness). Patients will receive the study drug as soon as possible after PCI, but at least within 3 hours after PCI. Prior to administration of the first gift, the nurse at the CCU administering the first dose will verify if patients still want to participate, and the patient information letter is handed over to the patient. Time of treatment will be recorded by the CCU nurse and verified by the investigator. In a later stadium following the PCI procedure, patients will sign the written informed consent.

### 5.2 Inclusion criteria

Inclusion criteria are:

- The diagnosis acute MI defined by chest pain suggestive for myocardial ischemia for at least 30 minutes, the time from onset of the symptoms less than 12 hours before hospital admission, and an ECG recording with ST- segment elevation of more than 0.1 mV in 2 or more leads.
- Successful primary PCI (post-procedural TIMI 2/3);
- At least one stent sized  $\geq 3.0$  mm;
- eligible for CMR-scan:
  - BMI  $<40$ ;
  - no metal objects in the body (pacemaker, ICD, etc);
  - no claustrophobia;
- Verbal followed by written informed consent.

### 5.3 Exclusion criteria

Patients will be excluded from this study for any of the following reasons:

- Rescue PCI after thrombolytic therapy;
- Need for emergency coronary artery bypass grafting;
- Kreatinin >177 µmol/L measured pre-PCI;
- General condition which, according to the clinical judgment of the investigator and/or treating physician, does not allow the patient to participate in the study;
- Inability to provide informed consent;
- Younger than 18 years;
- Mechanical ventilation;
- Diabetes;
- Prior myocardial infarction;
- Contra-indication to metformin (see safety);
- The existence of a life-threatening disease with a life-expectancy of less than 6 months.

## 6. RANDOMIZATION AND REGISTRATION

### 6.1 Randomization

The Department of Pharmacy will supply the medication per patient blinded to both investigator and patient. Every set of medication will have a number. This number corresponds to the case report form (CRF) number. This CRF number will be the identification of the patient throughout the trial. The number for the study medication assignment must be recorded in the subject case report form (CRF). In the event a subject drops out prior to randomization, the subject's number will be re-used. Once a set of medication is randomly assigned to a patient, it will never be re-used. Randomization records are never re-used. Randomization data are kept strictly confidential; and are accessible only to authorized persons ([name], Department of Pharmacy), until the time of unblinding. Only when all patients have reached the primary efficacy measure (endpoint), the data file verified and the protocol violations determined, the database will be locked, after which the drug codes will be broken and made available for data analysis. Independent physicians and/or research nurses, who are blinded for treatment allocation, will perform follow-up visits T4 and T5. The endpoint adjudication committee will, who also will remain blinded after database lock, will assess all clinical endpoints. Analysis of data collected after database lock during will be done when all patients have reached a visit (either T4 or T5).

Unblinding of treatment in case of emergency can be done via the in-house pharmacy. An exception for unblinding the data will be made for the DSMB (for details: see attachment: DSMB charter). The contact procedures/results prior to unblinding, the events precipitating the unblinding, necessary contacts thereafter, and study status of the subject whose trial treatment was disclosed must be documented by the investigator and maintained in the study files.

Randomization will be performed by Stichting Apotheek Haagse Ziekenhuizen. In 63 blocks of 6 and 1 block of 2 patients, metformin 500mg 2dd1 and placebo 2dd1 will be randomized. After the PCI procedure and after verbal informed consent, patients will receive the study medication (metformin

500mg 2dd1 or placebo 2dd1) double blind. The investigator confirms the randomization by recording it in a dedicated listing which will be archived in the Investigator Site File.

## **6.2 Registration**

Selected data of potential candidates will be collected in a dedicated computerized database (Oracle Clinical ©). The trial coordination center will provide this computerized database. Data will be inserted in the database by cardiologists and research personnel. Data will be collected during initial hospitalization, from patient files, by telephone contacts, and from outpatient's visits. The database will contain baseline characteristics, interventional data, medication use, ECG-characteristics, CMR characteristics, laboratory data and clinical data. The database will be managed by the trial coordination center and the researchers.

## **7. TREATMENT OF SUBJECTS**

### **7.1 Before PCI**

In the phase before admission to the catheterization laboratory the patient will receive the following medical therapy according to current international guidelines:

- aspirin (a bolus of 300 mg if not already being taken, followed by 80 to 100mg/24 hours);
- intravenous heparin/low molecular weight heparin according to a scheme based on weight;
- thienopyridines;
- glycoprotein IIb/IIIa inhibitor: according to a scheme based on weight.

### **7.2 PCI procedure**

All patients will be transported to the catheterization laboratory as soon as possible after admission to the hospital. At admission blood will be drawn from the patient by vena puncture for standard lab analysis. After gaining arterial access at the catheterization laboratory, both coronary arteries will be visualized. If the coronary anatomy of the culprit lesion is suitable for percutaneous intervention, PCI will be performed. Primary treatment of the ischemia related coronary artery will consist of thrombus aspiration followed by stent implantation (at least one stent sized  $\geq 3.0\text{mm}$ ). Additional balloon angioplasty will be performed when necessary. Thrombus aspiration will be performed using an aspiration device (CE, Medtronic Corporation, Santa Rosa, California, USA).

### **7.3 After PCI procedure**

Standard therapies after PCI will be administered according to international guidelines. Standard therapies include aspirin 80 or 100mg, thienopyridines, beta-blockers, lipid lowering agents (HMG-CoA-reductase inhibitors), and angiotensin converting enzyme inhibitors or angiotensin-II receptor blockers. These medications are likely to be protective in most patients.

Patients with new-onset diabetes will be treated according to international guidelines.

All medication used will be recorded in the eCRF (Oracle Clinical ©).

#### **7.4 Investigational product/treatment**

After successful PCI patients will be transferred to the CCU. After arrival all inclusion and exclusion criteria will be assessed, especially kreatinin concentration. Metformin tablets will be administered orally at 500 mg twice daily for 4 months or matching placebo tablets will be administered twice daily, blinded to both patients and cardiologists.

#### **7.5 Co-intervention**

Co-intervention is not applicable. No specific restrictions to co-medication apply. Permitted co-medication includes e.g. stable, appropriate pharmacologic therapy for coronary artery disease, heart failure or heart rhythm disorders (e.g. angiotensin converting enzyme inhibitors, angiotensin receptor blockers, beta blockers, anticoagulant drugs, platelet inhibitors, calcium antagonists, anti-arrhythmics, diuretics, HMG-CoA reductase inhibitors, nitrates, alfa blockers). The investigator may change the dose or add/discontinue any of the medications identified above if in the opinion of the investigator such a change is medically necessary. Cardiovascular medication at hospital admission, at hospital discharge, and during the outpatient clinic visits will be recorded in the eCRF.

## **8. INVESTIGATIONAL MEDICINAL PRODUCT**

### **8.1 Name and description**

Metformin, a biguanide hypoglycaemic agent used in the treatment of type 2 DM, improves glycaemic control by improving insulin sensitivity and decreasing intestinal absorption of glucose.

Metformin (hydrochloride) is a registered medicinal product (see attachment Summary of Product Characteristics).

The study medication, both metformin and placebo, will be provided by Stichting Apotheek Haagse Ziekenhuizen. For the metformin a Summary of Product Characteristics form is added as an attachment. An Investigational Medical Product Dossier of the placebo is also added by Stichting Apotheek Haagse Ziekenhuizen.

### **8.2 Summary of findings from non-clinical studies**

The ability of metformin therapy to promote the activation of AMPK, the phosphorylation of eNOS, the reduction of biomarkers reflecting inflammation, the improvement of endothelial dysfunction, the inhibition of the formation of AGEs and RAGE, the inhibition of mPTP formation, the suppression of DPP-4 activity, and increase NO bioavailability provides numerous potential cardioprotective actions in the setting of heart failure, such as vasodilatation and the inhibition of oxidative stress and apoptosis. All of these actions, in addition to the effects of NO on the mitochondria, could account for the improvements in left ventricular function following metformin treatment. In particular, the effects of eNOS on hemodynamics could play an important role in providing prolonged changes in afterload and coronary blood flow regulation, which could then promote left ventricular function and improve left ventricular ejection fraction.

### **8.3 Summary of findings from clinical studies**

Metformin decreases blood glucose by enhancing insulin sensitivity, inducing greater peripheral uptake of glucose, and decreasing hepatic glucose output while lowering plasma insulin

concentrations (21;22). In the DIGAMI II glucose lowering by means of metformin did not influence mortality but was related to a lower proportion of non-fatal cardiovascular events (24). The latter finding is in agreement with the UKPDS, but in this study metformin did also have a mortality lowering effect, probably because of inclusion of more patients and longer follow-up (21). In an observation by Anselmino and colleagues, metformin-treated patients had a trend towards lower 1-year mortality, combined cardiovascular endpoints, and revascularization procedures while the use of sulfonylureas was neutral in this respect (29). In four retrospective, non-randomized cohort studies of diabetics with heart failure, treatment with metformin was associated with better outcome than treatment with other glucose lowering drugs (10;30-32).

Metformin treatment resulted in a 30% reduction of diabetes related endpoints and mortality compared to other glucose lowering therapies, lowering blood glucose to equal levels (21). Thus, the cardioprotective effects of metformin can not be attributed to glucose lowering effects alone (34).

#### **8.4 Summary of known and potential risks and benefits**

The possible occurrence of a severe lactic acidosis is known as one of the adverse effects of metformin. In contrast with the huge number of treated patients, metformin-associated lactic acidosis (MALA) is rare, with an estimated incidence of three per 100,000 metformin-treated patients per year, but is associated with a high mortality rate, averaging 50% (21;22). In most cases, MALA occurs in a previously treated type 2 diabetic patient when a concurrent disease induces an acute renal failure leading to metformin accumulation. The association between metformin and decreased renal perfusion in MALA lead to the contraindication of metformin in patients with heart failure and decreased renal failure. The causative mechanism has been disputed by Lalau et al (2001) (23).

According to current guidelines metformin therapy is contraindicated in patients with acidosis, renal insufficiency or heart failure with NYHA classification II or higher ([www.fk.cvz.nl](http://www.fk.cvz.nl)).

### **8.5 Description and justification of route of administration and dosage**

The route of administration of the metformin 500 mg 2dd1 tablets is oral. The bioavailability is approximately 50 to 60 %. Withdrawal of study drug can be considered if the study drug is not tolerated or otherwise indicated in a specific patient (see withdrawal criteria). No other modifications to study drug can be made.

Normal starting dosage of metformin for treatment of diabetes type II varies from 500mg once daily to 500mg twice daily. Maximum dosage of metformin for treatment of diabetes type II is 3000mg divided over 3 gifts. In our study protocol we chose a dose of 500mg administered twice daily. Based on figures from the EASD 2009 guidelines (3) metformin leads to side effects, most all gastrointestinal discomfort, in 30% of patients and results in discontinuation of 2-5% of patients started on metformin therapy. The side effects are, equal to the antihyperglycaemic effects, dose-dependent. Since the time window of administration of metformin is relatively short (4 months) for titration, metformin will be dosed in one uniform dosage. Most importantly, there is no evidence for a dose-dependent relation between metformin and the supposed cardioprotective effects. The dosage of metformin administered in the animal experiments (34-36) was high (metformin 250mg/kg/ml) compared to dosages normally administered in humans (8-45mg/kg/day). However, animal experiments demonstrated that relatively high dosages of metformin were necessary for the drug to exert its antihyperglycaemic effects in hyperglycaemic rats. Therefore, it might be deducted that the non-dose-dependent cardioprotective effects of metformin show at a dosage of 500mg metformin twice daily.

### **8.6 Dosages and method of administration**

Metformin 500mg 2dd1 tablet oral.

### **8.7 Preparation and labeling of Investigational Medical Product**

A white film coated double convex tablet formation of metformin hydrochloride (see attachments) in strengths of 500mg and a visually matching placebo tablet will be used for the 4 months double-blind treatment phase of the study. All study drugs will be supplied by Stichting Apotheek Haagse Ziekenhuizen and released for use according to Stichting Apotheek Haagse Ziekenhuizen standard operating procedures. All study drugs should be stored at room temperature of 20 to 25 degrees Celsius. The drugs will be dispensed during hospital admission and at the visit to the outpatient clinic at 6 weeks after randomization. Each treatment kit will contain blister cards, each containing a 1 week supply of study drug (14 tablets). Study drug labeling will include the following: sponsor's name, sponsor's address, sponsor's telephone number, route of administration, content ("metformin 500mg or placebo"), number of tablets, expiration date, "keep out of reach of children", "clinical trial medication", batch code, protocol number, name and address of principal investigator, patient number, and directions for use; according to Annex 13 of Good Manufacturing Practice. The study drug label will be supplied by Stichting Apotheek Haagse Ziekenhuizen (see attachment)

### **8.8 Drug accountability**

The investigator will accurately record the amount of study drug received, dispensed, consumed or administered, and returning during the study period. An accurate record of the date and amount of the study drug dispensed to each subject must be available for inspection at any time. Dispensed medication will be recorded in a dedicated folder. Drug supply accountability, based on tablet counts, will be performed at the conclusion of the study, recorded on the appropriate CRF and the subject's source documentation. All unused study drug will be returned to the Department of Pharmacy of the UMCG, to destroy the study drugs according to accepted standards of Good Clinical Practice, the protocol and all applicable government laws and regulations and ICH guidelines governing the performance of clinical investigations. Drug accountability will be reviewed by the Department of Pharmacy of the UMCG during site visits and at the completion of the trial. The

investigator must not destroy any drug labels, or any partly-used or unused drug supply. All drug supplies are to be used only for this protocol and not for any other purpose. Partly-used or unused study drug will be destroyed in accordance with local, state, and federal regulations.

### **8.9 Compliance**

Patients that used >80% of the study medication they were supposed to use, are considered to be compliant. A protocol violation will be reported if patients are non-compliant.

## **9. OUTCOME PARAMETERS AND SUBGROUPS**

### **9.1 Outcome parameters**

#### **9.1.1 Main study outcome parameter**

The primary endpoint (primary efficacy parameter) is to evaluate the effect of metformin treatment (in the intention-to-treat analysis) after a successful PCI for a first acute MI on left ventricular ejection fraction measured with CMR imaging at 4 months after the PCI procedure (as described in detail).

#### **9.1.2 Clinical secondary study outcome parameters**

Incidence of a cardiovascular event within 4 months and after long-term follow-up: defined as cardiovascular death, re-infarction (STEMI or Non-STEMI), re-intervention by PCI (target lesion revascularization, target vessel revascularization, or non-target vessel revascularization) or CABG, stroke (CVA, no TIA) and combined endpoints. MACE is defined as death, re-infarction and target lesion revascularisation.

Mortality will be divided into cardiac and non-cardiac. Cardiac death will be divided into three categories: heart failure, sudden death and other. A cardiologist will confirm deaths from cardiovascular causes by examining medical records obtained from hospitals and attending physicians or from attending general practitioner if the patient died at home. Sudden cardiac death will be defined as either witnessed, or un-witnessed, cardiac arrest without evidence of circulatory collapse, such as hypotension, exacerbation of congestive heart failure, or altered mental status, before the disappearance of the pulse or abrupt collapse occurring within one hour of the onset of the symptoms that resulted in death. Death due to heart failure will be defined as death due to clinically end-stage heart failure during hospital admission or by exacerbation of congestive heart failure reported by an attending general practitioner. For all these deaths, no probable non-cardiac cause should be suggested by the history or autopsy.

| CLINICAL SECONDARY ENDPOINT       | CLASSIFICATION | SUBGROUP |
|-----------------------------------|----------------|----------|
| Death                             | 1              |          |
| - Cardiac                         |                | A        |
| - All Cause                       |                | B        |
| Recurrent myocardial infarction   | 2              |          |
| - STEMI                           |                | A        |
| - Non-STEMI                       |                | B        |
| Recurrent coronary intervention   | 3              |          |
| - target lesion PCI               |                | A        |
| - target vessel PCI               |                | B        |
| - non target vessel PCI           |                | C        |
| - CABG                            |                | D        |
| Cerebrovascular accident (CVA)    | 4              |          |
| Non-elective hospitalisation for: | 5              |          |
| - Heart failure                   |                | A        |
| - chest pain                      |                | B        |
| ICD implantation                  | 6              |          |
| New onset diabetes                | 7              |          |
| Prediabetes                       | 8              |          |

Tabel 1: Clinical secondary endpoints.

A non-elective hospitalization (defined as an overnight stay, with different dates for admission and discharge) for clear symptoms of heart failure within 4 months and after long-term follow-up will be recorded. Furthermore, non-elective hospitalization (defined as an overnight stay, with different dates for admission and discharge) for chest pain will be recorded as an endpoint. Implantation of an internal cardiac defibrillator (ICD) will be recorded as an endpoint. Hospitalization for other reasons than heart failure or chest pain will not be recorded as an endpoint. Whenever a patient undergoes an elective PCI, CABG, or ICD implantation, or has a recurrent myocardial infarction or stroke, the patient is (likely to be) hospitalized. Therefore, in case of these events, the hospitalization itself will not be recorded as a separate endpoint. New onset diabetes and prediabetes, as defined by the guidelines (see Appendix 14.2) will be recorded as an endpoint. Whenever new onset diabetes is

diagnosed, patients will be treated by an endocrinologist at University Medical Center Groningen according to current guidelines. Treatment for diabetes will be additional to study treatment. Visits for treatment will be separate from study visits.

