## **9.3 Study procedures**

### **9.3.1 Baseline characteristics and clinical outcome**

Baseline characteristics that will be collected include age, gender, time of symptom onset of first and last symptoms, time of admission, history of CABG, previous PCI, stroke and MI, positive family history for cardiovascular diseases, existence of diabetes, hypertension, smoking status, heart rate,

systolic and diastolic blood pressure, weight and length. Current treatment at admission of the patients to the hospital will be recorded.

Death, reinfarction, and ischemia driven target vessel revascularization will be recorded at 30 days and at 4 months and after long-term follow-up. Follow-up information will be obtained from hospital records, written correspondence and/or telephone interviews with the patient.

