### 10.3 Adverse and serious adverse events

Adverse events are defined as any undesirable experience occurring to a subject during a clinical trial, whether or not considered related to the investigational procedure. All adverse events reported spontaneously by the subject or observed by the investigator or his staff will be recorded. Disease related adverse events, which are clearly related to the underlying condition of the patient and are not related to the intervention, will only be reported 6 monthly to the METC.

A serious adverse event is any untoward medical occurrence or effect that:

- results in death;
- is life threatening (at the time of the event);
- requires hospitalization or prolongation of existing inpatients' hospitalization;
- results in persistent or significant disability or incapacity;
- is a new event of the trial likely to affect the safety of the subjects, such as an unexpected outcome.

Since metformin is a widely used medicine which adverse effects have been described in detail, serious adverse events which are common in patients suffering from myocardial infarction which have no known association with the intervention ("disease related adverse events") will be reported 6 monthly to the METC. All serious adverse events with a known association with metformin will be reported to the accredited METC that approved the protocol, according to the requirements of that METC. Serious adverse events that are used to assess safety by the DSMB, which include death, re-MI, target vessel revascularization, worsening renal failure and lactic acidosis will be reported to the METC at all times.

Subjects transferred to other hospitals (referring hospitals) after PCI, which is standard care, will not be considered as an SAE. For logistical reasons, the discharge date from the UMCG will be used to plan the subsequent study visits (T1 – T5). The actual dates that the patients are discharged from the referring hospitals will be collected afterwards and recorded in the database as date of discharge.

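### Re-intervention counts every later PCI or CABG, including elective ones, with no exclusion for procedures planned on the index angiogram before allocation; this attenuates a secondary endpoint.

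*Protocol*

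**What the plan says.** Section 9.1.2 defines the cardiovascular-event endpoint to include "re-intervention by PCI (target lesion revascularization, target vessel revascularization, or non-target vessel revascularization) or CABG". Table 1 repeats this as class 3, with subclasses A to D for target lesion PCI, target vessel PCI, non-target vessel PCI and CABG. Section 2.2 also lists re-PCI and CABG without qualification. None of these places requires the procedure to be unplanned or driven by ischaemia.

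The rule on admissions in Section 9.1.2 begins "Whenever a patient undergoes an elective PCI, CABG, or ICD implantation, or has a recurrent myocardial infarction or stroke" and concludes that "in case of these events, the hospitalization itself will not be recorded as a separate endpoint". The elective procedure therefore stands as an event and only the accompanying admission is dropped. Class 5 of the same table does carry a qualifier: "Non-elective hospitalisation for" heart failure or chest pain.

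Three further places name a revascularisation event:

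- Section 9.1.2: "MACE is defined as death, re-infarction and target lesion revascularisation".
- Section 9.3.1: "Death, reinfarction, and ischemia driven target vessel revascularization will be recorded at 30 days and at 4 months", and after long-term follow-up.
- Section 10.3, among the serious adverse events that the DSMB uses to assess safety: "death, re-MI, target vessel revascularization, worsening renal failure and lactic acidosis".

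**The concern.** A procedure decided before a patient receives study drug carries no information about the drug. Counting it as an outcome adds the same expected number of events to each arm, raises both event rates, and moves the risk ratio towards 1. Re-intervention is one of the clinical outcomes named in the protocol summary, so a diluted result could be read as absence of effect when the endpoint could not have shown one.

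The differing revascularisation terms are a separate matter. They dilute nothing, but they leave the Endpoint Adjudication Committee (EAC), whose assessments feed the DSMB (Section 10.7), without one definition of revascularisation to apply.

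**Working it through.** **Can a planned procedure predate allocation and still be counted?**

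1. Section 7.2: both coronary arteries are visualised, and primary treatment is of the ischaemia-related artery. Disease elsewhere is therefore known at the index procedure.
2. Sections 5.1 and 6.1: study medication follows the PCI.
3. Section 5.3: of CABG, only the need for an emergency operation is an exclusion. A patient for whom a later elective CABG or non-culprit PCI is intended can be enrolled.
4. Section 9.1.2: that later procedure falls in class 3B, 3C or 3D, and being elective does not remove it.
5. Section 10.7: the EAC assesses all endpoints, but the protocol gives it no rule for planned procedures.

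**Does this touch the plan's own sample size?** Section 11.3.1 gives N = (1.96 + 0.84)² × 2 × (9²/3²) = 7.84 × 18 = 141 per group, 282 in total. Allowing for 26% missing, 282/0.74 = 381.1, rounded up to 382, against 380 stated. The figure reproduces and rests on LVEF alone, so it does not change.

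**How much attenuation?** The protocol gives no rate for re-intervention, planned or unplanned, so the rates below are assumptions. Let r be the risk of an unplanned event in an arm and s the share with a planned procedure, equal in both arms and independent of r. The counted risk is 1 − (1 − s)(1 − r). The difference between arms shrinks by the factor (1 − s), while both risks rise.

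Power is by the normal approximation for two proportions, n = 190 per arm (380/2), two-sided 0.05: Φ{[d − 1.96√(2p̄(1 − p̄)/n)] / √[(p₁(1 − p₁) + p₂(1 − p₂))/n]}, where d = p₁ − p₂ and p̄ is their mean.

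Assumption A: r = 8% control, 5% metformin.

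| s | Control | Metformin | Risk ratio | Difference | Power |
|---|---|---|---|---|---|
| 0 | 8.0% | 5.0% | 0.625 | 3.0 points | 22% |
| 10% | 17.2% | 14.5% | 0.843 | 2.7 points | 11% |
| 20% | 26.4% | 24.0% | 0.909 | 2.4 points | 8% |
| 30% | 35.6% | 33.5% | 0.941 | 2.1 points | 6% |

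For example, at s = 10% the control risk is 1 − 0.90 × 0.92 = 0.172, the metformin risk is 1 − 0.90 × 0.95 = 0.145, and 0.145/0.172 = 0.843.

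Assumption B, deliberately more favourable: r = 12% control, 6% metformin.

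| s | Control | Metformin | Risk ratio | Power |
|---|---|---|---|---|
| 0 | 12.0% | 6.0% | 0.50 | 53% |
| 5% | 16.4% | 10.7% | 0.65 | 37% |
| 10% | 20.8% | 15.4% | 0.74 | 28% |
| 20% | 29.6% | 24.8% | 0.84 | 18% |
| 30% | 38.4% | 34.2% | 0.89 | 13% |

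**Revascularisation terms side by side.**

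| Place | Term |
|---|---|
| 9.1.2, cardiovascular event and Table 1 | any target or non-target PCI, or CABG |
| 9.1.2, MACE | target lesion |
| 9.3.1, follow-up | ischaemia-driven target vessel |
| 10.3, DSMB safety events | target vessel, no qualifier |

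**The case against.** The strongest reply is that any revascularisation is a recognisable endpoint, stated alike in Section 2.2, the text of Section 9.1.2 and Table 1, and that limiting it to ischaemia-driven events would be a different endpoint, not a correction. That stands, and the fix below does not ask for it. It removes only procedures documented as planned before allocation.

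It is also fair that the protocol never mentions staged procedures or says when a later one is decided, and that the sentence on elective procedures is there to avoid counting an admission twice. The inclusion of planned procedures follows from the broad definition, the wording on elective procedures and the absence of an exclusion; how often it would happen is unknown. A rule might sit in an analysis plan or in adjudication instructions that are not shown, but the definition as written counts these procedures.

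The practical stakes are modest. Section 11.3 calls the trial a proof of concept powered on LVEF, and under either assumption above power for re-intervention is low even with planned procedures removed. Table 1 codes the subclasses separately, so they can be reported apart.

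A reader might go further in three ways that the protocol does not support:

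- That the DSMB sees a different MACE from the one finally reported. Section 10.3 gives an open-ended list of safety events, including renal failure and lactic acidosis. It does not call the list MACE or make it a composite.
- That Section 9.3.1 restricts recording to ischaemia-driven target vessel procedures. It says these will be recorded, not that nothing else will be, and Table 1 sets out the other classes.
- That the differing terms cause the dilution. Only counting planned procedures does that.

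**Conclusion.** The point holds for overall re-intervention (class 3) and the broad cardiovascular-event composite. As written, both count procedures that treatment cannot affect. The result is attenuation and loss of power, not a shift in favour of either arm, because under blinded randomisation planned procedures are balanced in expectation.

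The size depends wholly on assumed rates. With planned procedures in 10% to 30% of both arms, a risk ratio of 0.63 would be seen as 0.84 to 0.94, and one of 0.50 as 0.74 to 0.89. If planned procedures are rare in this population, the effect is small.

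MACE is largely protected because it uses target lesion revascularisation, which a later non-culprit PCI does not enter. The LVEF primary endpoint and the total of 380 are untouched. The differing revascularisation terms are a separate fault of consistency that holds whatever the rate of planned procedures.

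**What to change.** 1. Add an eCRF field, completed before allocation, stating whether a further PCI or CABG is planned on the index angiogram and, if so, which.
2. State in Section 9.1.2 and Table 1 that procedures so documented do not count in class 3 or in the cardiovascular-event composite. They can be tabulated separately by arm.
3. Give the EAC this rule in writing. Because the field is completed before allocation and adjudication is blinded, the exclusion cannot depend on treatment.
4. Reconcile the revascularisation terms in Section 9.1.2 (MACE), Section 9.3.1 and Section 10.3, or say why the safety list is meant to differ.

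The cost is one data field, some endpoint wording and one adjudication instruction. The downside is fewer counted events. A procedure decided after allocation would still count, so some dilution may remain.
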